### Pre-training data collection

Health professionals who agree to take part will be asked to approach eligible family members to ask for consent to be contacted by the study team about completing two surveys about their baby’s sleep. Health professionals will show eligible family members a study details postcard, inviting them to take part in the study. For family members with literacy difficulties or where they do not speak English, study information can be read with support from the health professional, Language Line, or another family member, if appropriate. We will ask health professionals to promote the surveys with caregivers at the first point of contact in the antenatal or early postnatal period or shortly after admission to a neonatal unit. Health professionals will be asked to record that they have passed details to the study team in the family member’s medical notes. Caregivers who contact the research team or give permission for their contact details to be shared by their health professional will be contacted by a member of the team with an information sheet and link to a short video explaining the study, giving the family time to think about participation, ask questions and go through full informed consent.

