### Intervention activities

When each health professional has sent us details for at least 5 caregivers or where we have reached the target of 90 caregivers completing the first survey, we will provide health professionals with full access to the new resources and training materials, with online support from the study team, via a named Baby Sleep Project Champion at each of the study sites. The training will be completed online, on a dedicated password-protected webpage, with full access to the online training video, the Baby Sleep Planner, animations, downloadable copies of the safer sleep milestones cards and downloadable flyers with QR codes for the Baby Sleep Planner and animations. We will also post hard copies of these flyers to health professionals individually on completion of the training. Health professionals will receive a certificate of completion of the training for their portfolio.

We will encourage health professionals to use the new resources primarily with caregivers who are eligible for extra support, with the same eligibility as before, though they will be different caregivers due to the baby’s age requirement. Eligible caregivers will be different for different teams, and for some it will be all their clientele, for example, family nurse partnership nurses and neonatal teams. Caregivers can see and use the resources without taking part in the study. We will ask health professionals to approach all those who have seen or used the resources to ask for consent to be contacted by the study team. We will ask health professionals to invite caregivers who have not previously seen the resources, so as not to contaminate the pretraining data collection, and we will allow time for a short gap before introducing the resources to reduce this risk. Where pretraining caregivers have completed both surveys, health professionals will be able to use the new resources with them if they wish to do so.

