### Sample size

Using 90% power and 5% significance, proportional differences between 13% and 24% will be detected (depending on the prevalence of the variable) using 90 respondents before and 90 respondents after the study. A much larger definitive study is planned, but these findings will at least give us reasonable CIs of the differences to help generate a future sample size calculation. We aim to recruit 40–50 health professionals in total, aiming for up to 10 neonatal staff, 25 health visitors and 15 family nurse partnership nurses. Each site will have a health professional champion and a clinical principal investigator.

We will ask health professionals to approach at least five caregivers each *before* the intervention training (asking for consent to be contacted by the research team) and five each *afterwards*, assuming a 30–40% sign-up rate of approximately 3–4 caregivers per health professional in total. We should be able to recruit approximately 90 caregivers before and 90 caregivers after the intervention, total number of caregivers approximately n=180. We expect the minimal loss to follow-up due to the voucher incentive for the second survey and will over-recruit slightly on the first survey (up to 95) to minimise this risk. Due to the long recruitment period, we will have time to monitor follow-up rates and adjust accordingly, if required.

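### The post-training approach rule is stated two ways; if the uncapped one governs, the mix of professionals and settings may differ between the pre- and post-training groups

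*Protocol article*

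**What the plan says.** **Post-training, first rule.** Under Sample size, professionals are asked to approach at least five caregivers before training and "five each *afterwards*, assuming a 30–40% sign-up rate". The expected yield is built on this: "assuming a 30–40% sign-up rate of approximately 3–4 caregivers per health professional in total", leading to about 90 caregivers in each phase.

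**Post-training, second rule.** Under Intervention activities: "We will ask health professionals to approach all those who have seen or used the resources to ask for consent to be contacted". No number per professional is given. Eligibility is described as unchanged: "with the same eligibility as before, though they will be different caregivers due to the baby’s age requirement". The same section says that for family nurse partnership nurses and neonatal teams this may mean everyone on their caseload.

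**Pre-training.** Under Pre-training data collection: "Health professionals who agree to take part will be asked to approach eligible family members to ask for consent to be contacted". Five is a minimum ("We will ask health professionals to approach at least five caregivers each"), with no maximum. The training is released on either of two conditions: "When each health professional has sent us details for at least 5 caregivers or where we have reached the target of 90 caregivers". The second condition counts first surveys returned across the whole study.

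**Analysis.** Integration of data sources and analysis plans to adjust for caregiver characteristics that differ significantly between the groups. It also compares data within and between sites to inform the context-mechanism-outcome configurations. The recruiting professional is not mentioned.

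**The concern.** The pre/post comparison uses different caregivers in the two phases, so it depends on both groups being drawn in the same way. Before training, a professional's contribution cannot depend on use of resources that have not been released. Afterwards, under the rule in Intervention activities, it can: someone who shows the resources to two families has two to approach, and someone who shows them to twenty has twenty. The rule for composing the sample would then change at exactly the point being compared.

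The protocol itself allows for uneven use. Its programme theory makes the professional's valuing of these conversations the triggering context, and the NoMAD data are to be examined for differences between roles and regions. The mix of settings also bears on the outcome: hazardous co-sleeping includes co-sleeping with an infant born before 37 weeks or under 2500 g, so the same behaviour may be counted more often where more such infants are recruited. Because the differences are meant to inform the size of a later definitive study, a shift in composition would carry forward.

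This is separate from the question of which caregivers, within one professional's caseload, engage with the resources.

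**Working it through.** **1. The plan's own figures.** Expected recruitment per phase = professionals × 5 approaches × sign-up rate.

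- 40 professionals: 40 × 5 × 0.30 = 60 to 40 × 5 × 0.40 = 80
- 45 professionals: 67.5 to 90
- 50 professionals: 75 to 100

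So 90 per phase is reached with 45 professionals at 40%, or 50 at 36% (50 × 5 × 0.36 = 90). Per professional, 10 approaches × 30–40% gives the stated 3–4 in total. The recruitment target therefore follows from the five-each rule. The stated detectable differences also reproduce approximately: with 90 per group, 90% power and two-sided 5%, 13.5 points at a baseline of 2% and at most 23.9 points near 38–40%. That calculation does not bear on who is approached.

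**2. The two rules side by side.** With exactly five approaches each and a common sign-up rate, every professional has the same expected weight. Under the seen-or-used rule, weight is proportional to the number of families shown the resources. The documents give no figure for variation in use, so everything in steps 3 and 4 rests on assumed inputs.

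**3. Illustration by professional.** Shift in the pre/post difference = change in heavy users' share × prevalence gap between families of heavy and light users. The pre-training share is set at 50%, which is a planning assumption only.

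- Heavy users at 60% afterwards, gap 10 points: (0.60 − 0.50) × 10 = 1.0 point
- Half show the resources to 15 families and half to 5: share 15/20 = 75%; gap 10 points: 0.25 × 10 = 2.5 points
- Half approach 10 and half approach 2: share 10/12 = 83%; gap 10 points: 0.333 × 10 = 3.3 points; gap 20 points: 6.7 points

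For scale, the standard error of the difference at an assumed prevalence of 20% is √(2 × 0.2 × 0.8/90) = 0.0596, or 6.0 points.

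**4. Illustration by setting**, using the protocol's upper targets of 10 neonatal staff, 25 health visitors and 15 family nurses. With five each, the neonatal share is 50/250 = 20%.

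- Only neonatal staff approach 15: 150/(150 + 125 + 75) = 150/350 = 43%. A 20-point gap gives 0.229 × 20 = 4.6 points.
- Neonatal staff and family nurses both approach 15: 150/(150 + 125 + 225) = 150/500 = 30%. A 20-point gap gives 0.10 × 20 = 2.0 points.

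The second case fits the protocol better, since it names both groups as ones whose whole caseload may be eligible.

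**5. Would the planned adjustment catch it?** NICU admission is collected. If it tracks neonatal recruitment, then with 90 v 90:

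- 20% v 43%: pooled 31.4%, standard error √(2 × 0.314 × 0.686/90) = 0.069, z = 0.229/0.069 = 3.3. Adjustment would be triggered.
- 20% v 30%: pooled 25%, standard error √(2 × 0.25 × 0.75/90) = 0.0645, z = 0.10/0.0645 = 1.55. It would not be triggered.

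**The case against.** A reader might infer that the post-training group will over-weight keen users while the pre-training group weights professionals equally, and that this will make the resources look better than they are. The documents do not support that reading, for four reasons.

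- **Pre-training equality is not secured.** Five is a floor, there is no cap, and release can come at 90 completed first surveys even if some professionals have sent fewer than five. Fast recruiters can dominate that phase too. Unequal weights before training do not, however, make the two phases alike.
- **Over-weighting is conditional.** It needs the rule in Intervention activities to govern, use to vary between professionals, and nothing else to limit numbers. If the words setting a minimum of five carry over to the post-training phase, the conflict narrows. It does not vanish, because a light user still has few families to approach under the seen-or-used rule.
- **Direction is unknown.** Nothing shows that heavy users had safer families beforehand. The resources are aimed primarily at caregivers eligible for extra support, so heavy users may serve higher-risk families, and a larger neonatal share could raise measured hazard.
- **Setting is partly covered.** Adjustment through NICU admission would catch a large neonatal shift, and comparison within sites would separate the three neonatal units from the two community providers. But the first depends on reaching significance and the second is exploratory.

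It is also fair to say that this is a realist evaluation preceding a larger study, not a confirmatory test. That lowers the stakes of any false-positive rate. It does not remove the need for one rule.

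**Conclusion.** The point holds in limited form. The two post-training rules differ and must be reconciled, and the recruitment arithmetic fits only the five-each rule. If the uncapped rule governs, the mix of professionals and settings may change between phases for a reason that operates only after training, and the planned adjustment is not certain to deal with it.

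The size cannot be derived from the documents. Under assumed variation in use and assumed prevalence gaps of 10 to 20 points, the illustrations give shifts of 1.0 to 6.7 points by professional and 2.0 to 4.6 points by setting, against a standard error of about 6 points. The direction could be either way. The reason to act is that the remedy is cheap, not that a bias has been shown.

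**What to change.** 1. Reconcile Intervention activities and Sample size into one approach rule, applied identically in both phases: consecutive eligible caregivers, with the same target of about five per professional. Allow topping up on the same terms in both phases if 90 is not reached. A hard cap of five is inadvisable, since it would yield only 60–80 per phase with 40 professionals, or 75 with 50 professionals at 30% sign-up.
2. Include setting (neonatal, health visiting, family nurse) or site as a prespecified term in every pre/post comparison, whether or not it differs significantly between the groups.
3. Report the numbers approached and recruited per professional in each phase, so that any change in mix is visible.

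Professional-level fixed strata should not be used: 90 caregivers from about 45 professionals is 90/45 = 2 per professional per phase, too sparse for a binary outcome.

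The cost is possibly slower post-training recruitment and one extra model term. Recruitment opened on 8 April 2024, so if the approach rule can no longer be changed, items 2 and 3 can still be adopted, provided the approaches were logged.

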### Health professional research activities

We will ask all health professionals who take part in the study to complete brief implementation (NoMAD) questionnaires^25 35^ at three timepoints (immediately following the training, 2 months post-training and 4 months post-training) and ask a subset to take part in a qualitative interview. NoMAD questionnaires allow us to investigate the implementation processes and behaviours of the professionals taking part in the study, which will require collective action to become an embedded part of postnatal care.

### Caregiver research activities

We will invite caregivers who give consent to take part to complete online surveys when their babies are 3–4 weeks old and again when they are 8–10 weeks old (or longer where there has been a hospital stay). Two timepoints will provide evidence of any sustained effects from the intervention and covers the period of greatest risk for SIDS, according to the most recent data.^1^ We will also invite a subset to take part in a qualitative interview, pursuing a range of background characteristics relevant to SUDI risk. Figure 3 shows the intervention and research activities for health professionals and caregivers taking part in the study.

**Figure 3 F3:**
[figure not shown]
Flowchart of evaluation study.

### Sample size

Using 90% power and 5% significance, proportional differences between 13% and 24% will be detected (depending on the prevalence of the variable) using 90 respondents before and 90 respondents after the study. A much larger definitive study is planned, but these findings will at least give us reasonable CIs of the differences to help generate a future sample size calculation. We aim to recruit 40–50 health professionals in total, aiming for up to 10 neonatal staff, 25 health visitors and 15 family nurse partnership nurses. Each site will have a health professional champion and a clinical principal investigator.

We will ask health professionals to approach at least five caregivers each *before* the intervention training (asking for consent to be contacted by the research team) and five each *afterwards*, assuming a 30–40% sign-up rate of approximately 3–4 caregivers per health professional in total. We should be able to recruit approximately 90 caregivers before and 90 caregivers after the intervention, total number of caregivers approximately n=180. We expect the minimal loss to follow-up due to the voucher incentive for the second survey and will over-recruit slightly on the first survey (up to 95) to minimise this risk. Due to the long recruitment period, we will have time to monitor follow-up rates and adjust accordingly, if required.

### Data collection

#### NoMAD questionnaires (post-training)

NoMAD questionnaires will be completed by participating health professionals at three timepoints (post-training, 2 months and 4 months) and will be used to assess implementation across each of the four domains of Normalisation Process Theory (coherence, cognitive participation, collective action and reflexive monitoring).^25^ These questionnaires will be analysed to look for differences between roles, regions and changes across each timepoint. Petal charts will allow us to visualise these findings.

#### Parental surveys (pre- and post-training)

Online self-efficacy measures and sleep surveys will be sent to caregivers at 3–4 weeks after birth and 8–10 weeks after birth (or longer where there has been a hospital stay). Surveys will be completed online (using JISC online survey platform), but can also be completed over the phone with a member of the research team or via an online interpretation service. We will also collect data on maternal age, parity, smoking/vaping during pregnancy, NICU admission, baby’s sex, birth weight, partner support, partner smoking status, usual infant sleep location/position and sleep location/position last night (reflecting the night immediately before the survey). The 13-item two-factor UPPSEISI will be used to measure parental self-efficacy. Our outcome measures will be the prevalence of non-supine sleeping positions and hazardous co-sleeping (co-sleeping with an infant on a sofa or in a bed with an adult who has consumed alcohol, smokes, has taken drugs that may make them drowsy or with an infant that was born before 37 weeks gestation or under 2500 g birth weight). A copy of the survey can be found in online supplemental file A. Survey responses to our main outcome data will be mandatory within the survey software.

#### Qualitative interviews (post-training)

Interviews with health professionals will take place 8–12 weeks after training in the intervention to give them time to have had experience with it with several families. Topic guides will be informed by our C-M-O configurations and initial programme theory (see online supplemental file B).

Caregivers in the intervention group will be invited to a semistructured interview via consent to be contacted collected in the survey. The topic guide will be informed by our C-M-O configurations and initial programme theory (see online supplemental file C).

### Integration of data sources and analysis

Data sources will be used to develop the programme theory by comparing and contrasting it with our initial programme theory. Data will be used to support, refine or refute this initial theory. We will begin by using our initial theory as a coding framework for the qualitative interviews (parent and professionals) analysis. This analysis will be done in NVivo using both inductive and deductive coding to allow for the identification of new conceptual themes not present in our initial programme theory. These themes will be discussed with the research team to develop C-M-O configurations. We will then use the quantitative data sources (NoMAD and parental surveys) to look for how they do or do not support these configurations. Parental surveys will be downloaded and anonymised and analysed to investigate differences in infant care practices relating to the intervention between pre- and post-training. We will investigate whether hazardous co-sleeping or non-supine sleeping as a usual practice or ‘last night’ changes between the two groups. These distinct measures will be documented separately. We will also compare parental self-efficacy between the two groups. As these surveys will be completed by caregivers of different babies, we will look closely at any differences in the characteristics of these individuals. Any characteristics that significantly differ between the groups will be adjusted for in the analysis. Data will be analysed using STATA to compare responses before and after the intervention is introduced, and proportional differences in outcome measures between 4 and 8 weeks. We will also compare subgroups of responses based on lower (<115) and higher (115+) risk scores using our recently developed risk scoring algorithm.^21^ Quantitative data will be compared within and between sites and between lower-risk and higher-risk participants to explore differences and inform the development of the C-M-O configurations. Normalisation Process Theory and the COM-B model will support cross-case comparisons of our C-M-O configurations to support the iterative development of the programme theory alongside the integration of data sources. The final programme theory will be presented in a diagram with a corresponding descriptive account. All data will be held on University of Bristol servers with access only available to the research team and analysed using STATA statistical software.^36^

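### Adjusting the pre/post comparison only for characteristics that differ significantly can leave real confounding, above all in hazardous co-sleeping

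*Protocol article*

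**What the plan says.** The section on integration of data sources and analysis compares hazardous co-sleeping, non-supine sleeping and parental self-efficacy between caregivers surveyed before and after staff training. It recognises that the groups are not the same people ("As these surveys will be completed by caregivers of different babies"), promises a close look at how they differ, and then sets the rule: "Any characteristics that significantly differ between the groups will be adjusted for in the analysis". No other adjustment is stated for this comparison. The risk score appears there only as a way to form lower- and higher-risk subgroups.

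The parental surveys section lists the characteristics collected. They include smoking or vaping in pregnancy, partner smoking, birth weight and neonatal admission. The same section counts co-sleeping as hazardous when it takes place "in a bed with an adult who has consumed alcohol, smokes" and also "with an infant that was born before 37 weeks gestation or under 2500 g birth weight", among other conditions.

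The sample size section plans on "90 respondents before and 90 respondents after the study" and states: "Using 90% power and 5% significance, proportional differences between 13% and 24% will be detected". It adds that the CIs of the differences are to help size a larger definitive study.

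**The concern.** A characteristic confounds the comparison when it is imbalanced and also predicts the outcome. A significance test on the imbalance ignores the second condition, and with groups of this size it detects the first poorly. A strong predictor with a moderate imbalance is likely to be left out, while a weak predictor with a chance imbalance is let in.

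Hazardous co-sleeping is a special case because fixed family characteristics are part of its definition. Suppose a share b of families bed-share, regardless of smoking or birth status. If the share of families with a defining hazard moves from h0 to h1, measured prevalence moves by b × (h1 − h0) with no change in anyone's behaviour. That could look like an effect of the resources or hide one. The resulting difference and CI would then feed the planning of the next study.

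**Working it through.** **Inputs.** From the protocol article: 90 per group, 5% significance, 90% power, detectable differences of 13 to 24 points. Assumed: two-sided tests, and 5% as the level meant by a significant difference. The article gives no confounder prevalences or outcome risks, so every value used for them below is an assumption.

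**1. The plan's own figure.** The formula is the pooled-variance normal approximation, with p̄ the mean of p1 and p2:

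power = Φ{ [|p2 − p1| − 1.96 √(2p̄(1 − p̄)/n)] / √([p1(1 − p1) + p2(1 − p2)]/n) }

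At n = 90, 38% versus 62% has power 0.903. The difference detectable with 90% power is 12.3 points from a 1% baseline, 13.5 from 2% and 23.9 from 40%. The 13 to 24 point range is reproduced.

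**2. The same formula applied to the imbalance screen.** For 25% versus 35%, p̄ = 0.30:
- 1.96 × √(2 × 0.30 × 0.70/90) = 0.134
- √((0.1875 + 0.2275)/90) = 0.0679
- power = Φ((0.100 − 0.134)/0.0679) = Φ(−0.50) = 0.31

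| True imbalance | Chance of being flagged |
|---|---|
| 10% vs 20% | 47% |
| 20% vs 30% | 34% |
| 25% vs 35% | 31% |
| 30% vs 40% | 29% |
| 20% vs 32% | 45% |

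For a characteristic present in about half of families, the observed gap must exceed 1.96 × √(0.5/90) = 14.6 points to qualify.

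**3. One confounder, no intervention effect** (assumed: 40% before and 30% after; outcome risk 40% with it and 5% without; 200,000 simulated studies). The crude bias should be 0.10 × 0.35 = 3.5 points, and the simulation gives −3.5. The screen flags the confounder in 29.5% of studies. The mean spurious difference is −1.6 points under the plan's rule and 0.0 with constant adjustment. The −1.6 comes from the 70.5% of studies in which the confounder is missed: 1.6/0.705 ≈ 2.3 points in each of those. Type I error is 5.4% under the rule and 5.0% with constant adjustment.

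**4. Five binary factors, no intervention effect** (assumed: each adds 12 points of risk to a 5% base; 4,000 simulated studies per scenario).

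| Imbalance | Crude bias expected | Left by the plan's rule |
|---|---|---|
| All five 25% vs 33%, same direction | 5 × 0.08 × 0.12 = 4.8 points | 2.5 to 2.7 points |
| All five 25% vs 29%, same direction | 5 × 0.04 × 0.12 = 2.4 points | 1.7 points |
| One factor 25% vs 33% | 0.08 × 0.12 = 1.0 point | 0.6 points |
| Four factors by 8 points, two each way | 0 | about 0.1 points |
| None | 0 | about 0.1 points |

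In the first scenario about 1.1 of the five factors are selected. Prespecified adjustment leaves 0.0 to 0.1 points, with a standard error of 0.060 against 0.061 under the rule. Type I error under the rule is about 6.5% in the first scenario and close to 5% to 6% in the others.

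**The case against.** Several points on the other side stand.

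- The study is an exploratory realist evaluation, a larger study is planned, and no confirmatory claim rests on this test.
- The rule is not useless. It catches large imbalances, and in the simulations above with a real net imbalance it removed between about a third and a half of the mean bias.
- Drift in case mix is limited by design. The same health professionals approach caregivers in both phases under the same eligibility. The planned within-site and risk-group comparisons could expose a shift. These safeguards reduce the problem, but they do not adjust the estimate.
- The worst simulated case needs five factors all moving the same way. Nothing in the article says that this will happen.

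A reader might also infer more than the article supports. The pre/post contrast is not the only quantitative comparison: NoMAD scores by role, region and time, the two survey timepoints, sites and risk groups are compared too. The argument from the outcome definition applies to hazardous co-sleeping and does not carry over to non-supine sleeping or self-efficacy. Nor are the test and CIs badly invalid because covariates are chosen from the data, since the inflation found above is small. The harm is a shifted estimate.

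**Conclusion.** The concern holds in a limited form. The rule can leave confounding in the main caregiver outcome comparison; it does not always do so. The firm part is the low power of the screen. At 90 per group a 10-point imbalance in a characteristic such as smoking would usually go unadjusted, and this follows from the protocol's own sample size with only the 5% two-sided level assumed.

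The size of the resulting bias is not firm. It is about 2.5 points when five factors are imbalanced 25% versus 33% in the same direction, and 0 to 2 points in the milder or mixed scenarios, against a standard error of about 6 points. Those figures rest on assumed prevalences and effects.

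This should be fixed. It does not undermine the study, but the differences and CIs are a stated deliverable and a better rule is readily available.

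**What to change.** Replace the sentence with a short fixed set, for example:

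> The pre/post comparisons will be adjusted, whatever the significance of baseline differences, for smoking in pregnancy, partner smoking, preterm or low birth weight (<2500 g), and neonatal admission or service type. Unadjusted and adjusted risk differences with CIs will both be reported, and group differences in characteristics will be shown descriptively.

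The adjusted difference for self-efficacy would be a mean difference. Gestation is not in the article's list of characteristics, although the outcome definition needs it, so the sponsor should confirm that it is recorded. If it is not, birth weight can be used.

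The existing risk score could replace the covariates that it overlaps with, and would keep the model small. Its components are not given in the article. It should be used only if the sponsor confirms that it contains no sleep practices that the intervention targets.

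The cost is one sentence and a few parameters, which matter if the outcome is rare. At an assumed 10% prevalence, 180 caregivers give 18 events. Four binary covariates plus group make five coefficients, or 18/5 ≈ 3.6 events each. A model of about eight parameters, as with terms for five sites, would have about two. The finding of no precision loss came from average risks near 20% to 25% without site terms and should not be carried over to a rare outcome. The set should therefore stay small, with standardisation or a penalised model if events are few.

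### The 13–24 point detectable difference assumes independent samples although the same sites and professionals supply both phases, and the stated 4-versus-8-week contrast cannot by itself show a sustained effect

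*Protocol article*

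**What the plan says.** **Precision.** The Sample size section states: "Using 90% power and 5% significance, proportional differences between 13% and 24% will be detected", the exact value "depending on the prevalence of the variable", with the range obtained "using 90 respondents before and 90 respondents after the study". It adds that "these findings will at least give us reasonable CIs of the differences to help generate a future sample size calculation". It mentions no clustering and no repeated measurement.

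**Who supplies the data.** Setting and context lists five sites: three neonatal units and two community providers. The Sample size section plans for 40–50 professionals across the neonatal, health visiting and family nurse partnership teams. Each professional approaches at least five caregivers before training and five after, so the same professionals and sites feed both phases with different caregivers.

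**Repeated surveys.** Each caregiver is surveyed at 3–4 and 8–10 weeks. Caregiver research activities gives the reason: "Two timepoints will provide evidence of any sustained effects from the intervention".

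**Analysis.** Integration of data sources and analysis says the data will be used to "compare responses before and after the intervention is introduced, and proportional differences in outcome measures between 4 and 8 weeks". Characteristics of caregivers that differ significantly between the groups are adjusted for. Data are also compared within and between sites to inform the programme theory. No test, model or variance estimator is named.

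**The concern.** There are three linked weaknesses.

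1. **Precision.** The detectable difference is given as if the 180 caregivers were unrelated. They are grouped by professional (about two per phase) and by site (about 18 per phase). In a before/after comparison within the same units, stable unit effects cancel and help precision, while unit-specific change between phases hurts it. The published range reflects neither. It matters because the confidence intervals are meant to feed the sample size of a larger study.

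2. **Adjustment.** Sites differ in kind. Prematurity and low birth weight are part of the hazardous co-sleeping definition, so prevalence can be expected to differ between neonatal units and community services. Leaving site or service to a significance test between groups means that a known design factor may drop out of the model.

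3. **Sustained effect.** A change between 4 and 8 weeks reflects the infant growing older as well as any fading of the intervention. Persistence is a question about whether the before/after effect at 8–10 weeks resembles that at 3–4 weeks. The article does not state that contrast.

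**Working it through.** **Step 1. Reproduce the stated range.** Inputs from Sample size: n = 90 per phase, 90% power, 5% significance (taken as two-sided; the article does not say). For two independent proportions with mean p̄ and difference d:

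n = [1.96·√(2p̄(1−p̄)) + 1.2816·√(p1(1−p1) + p2(1−p2))]² / d²

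- 38% v 62%: [1.96 × 0.7071 + 1.2816 × 0.6864]² / 0.24² = 5.13 / 0.0576 = 89.1, so 90 per group. The upper end of 24 points is reproduced.
- 1% v 14% needs 85 per group and 2% v 15% needs 95, so 13 points corresponds to a lower rate of about 1–2%.
- A one-sided test tops out at about 21.6 points and does not fit.

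The range therefore contains no design effect and no pairing.

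**Step 2. Add clustering shared by both phases.** With m caregivers per cluster per phase:

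DE = 1 + (m − 1)·ICC − m·ICC·CAC

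Here CAC is the between-phase correlation as a fraction of the within-phase correlation (1 = fully stable cluster effects, 0 = unrelated from phase to phase). The effective n is 90/DE. The article gives neither ICC nor CAC; all values below are assumptions.

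*Professional*, m = 90/45 = 2, ICC 0.10:
- CAC 1: 1 + 0.10 − 0.20 = 0.90
- CAC 0: 1 + 0.10 = 1.10

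The standard error changes by about 5% either way (√0.90 = 0.95, √1.10 = 1.05).

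*Site*, m = 90/5 = 18, ICC 0.05, solving the Step 1 formula for d at 90/DE (rates symmetric about 50%; 23.9 points with no clustering):

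| CAC | DE | Effective n per phase | Detectable difference |
|---|---|---|---|
| 1 | 1 + 0.85 − 0.90 = 0.95 | 94.7 | 23.3 points |
| 0.8 | 1 + 0.85 − 0.72 = 1.13 | 79.6 | 25.4 points |
| 0.5 | 1 + 0.85 − 0.45 = 1.40 | 64.3 | 28.1 points |
| 0 | 1 + 0.85 = 1.85 | 48.6 | 32.2 points |

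The last row is an extreme. At the low-prevalence end (lower rate 2%, 13.5 points if independent), the first three rows give 13.0, 14.8 and 17.4 points. At a site ICC of 0.02, DE is 0.98 (CAC 1) or 1.05 (CAC 0.8), which is negligible.

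**Step 3. The two surveys.** For 4 v 8 weeks in 90 caregivers at an assumed 20% prevalence, the 95% half-width is 1.96·√(2 × 0.16 × (1 − ρ)/90), where ρ is the within-caregiver correlation:
- ρ = 0 (pairing ignored): 11.7 points
- ρ = 0.3, 0.5, 0.7: 9.8, 8.3, 6.4 points

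This contrast has no before/after comparison in it, so a narrow interval would still not separate ageing from fading. The contrast that does is the change in the after group minus the change in the before group. Its half-width is √2 times the paired value: at ρ = 0.5, 1.41 × 8.3 = 11.7 points. Persistence can be estimated, but imprecisely.

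**The case against.** The strongest reply is that the article names no test or variance method. It is a condensed account, and the analysis plan may handle clustering and pairing correctly. This stands. A reader might infer from the sample-size text that the analysis will treat the data as independent and that its confidence intervals are therefore wrong; the article does not say so. Nor is the direction of any error known, since the design effect falls on either side of 1.

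Four further replies have force:

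- **One age at a time.** The two groups are different caregivers, so a before/after comparison at a single age has one response per person and is not invalidated by the second survey.
- **Precision gain.** A reader might expect a joint model to cut the standard error by 13%, since √((1 + 0.5)/2) = 0.87. That applies only to an effect averaged over both ages with an assumed correlation of 0.5. With complete data, the effects at each age gain essentially nothing.
- **Limits of site adjustment.** Site terms remove stable differences but not site-specific drift between phases, and five sites are too few for reliable site-clustered inference.
- **Existing comparator.** The pre-training group is surveyed at both ages, so the data needed to separate ageing from fading will exist.

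The last reply is also why the sustained-effect point survives: the data allow the right contrast, but the stated analysis is the 4-versus-8-week difference. Likewise, exploring results within and between sites is not the same as adjusting the before/after estimate for site.

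**Conclusion.** The point holds as a weakness in what the article states, not as a demonstrated error in its results. The 13–24 points is an independent-samples figure for a design with shared clusters. Under an assumed site ICC of 0.05, its upper end is about 23 points with stable site effects and about 28 with a between-phase correlation half the within-phase value. At professional level the change is about 5% in the standard error. No single corrected figure can be given, because the documents provide no ICC.

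The significance-based adjustment rule and the 4-versus-8-week contrast need no assumed correlation to be questioned. The first can leave out a known design factor; the second cannot on its own support the claim of a sustained effect. It would be too strong to conclude that the study is underpowered or that its intervals are invalid. In an exploratory evaluation preceding a larger study this is worth correcting but not critical, and the main consequence is for the sample-size calculation that follows.

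**What to change.** 1. **Before/after models.** Include site in every model regardless of significance, or service type if events are sparse. Cluster standard errors by referring professional where that link is available.
2. **Persistence.** Fit one GEE or mixed model per outcome with phase, survey and phase × survey, accounting for the two surveys per caregiver. Report the before/after effect at each age and judge persistence from those and the interaction. Present the 4-versus-8-week difference as descriptive.
3. **Sample size text.** Say that 13–24 points assumes independence, and give the range under stated ICC and CAC assumptions, as in the table above.

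**Cost.** No extra participants or survey items are needed; most of the change is wording. The link from caregiver to professional must be kept through anonymisation, and caregivers who contact the team themselves may need to be asked who referred them. The interaction will be imprecise. Five sites cannot support a correction for site-specific drift between phases, so that should be stated as a limitation.
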